### Primary endpoint

To evaluate whether the addition of an ablative microboost to the macroscopic tumor within the prostate increases the five-year freedom from biochemical failure rate compared to the current standard of care. Biochemical failure is defined according to the Phoenix definition as a PSA rise of 2 ng/mL above the nadir PSA level [42]. The PSA level will be measured every six months until 10 years after treatment.

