### Secondary endpoints

Secondary endpoints are treatment-related toxicity, QoL and disease-specific survival. Treatment-related toxicity is measured by the Common Toxicity Criteria for adverse events version 3.0 (CTCAE) [43]. The following adverse events are scored: urinary frequency/urgency, urinary retention, bladder spasms, urinary incontinence, genitourinary hemorrhage, dysuria, rectal or perirectal pain, proctitis, diarrhea, flatulence hemorrhoids, anal incontinence, erectile dysfunction. The physician in attendance scores the complaints before treatment, acute toxicity (weekly during treatment and 4 weeks after treatment) and late toxicity (every six months until 10 years after treatment). All symptoms are registered even if they occur only on one single occasion. Grade > 2 is considered severe toxicity.General health-related QoL is measured using the RAND-36 generic health survey [44], cancer-specific QoL using the European Organization for Research and Treatment of Cancer (EORTC) core questionnaire (QLQ-C30) [45], and the prostate tumor-specific QoL using the EORTC prostate cancer module (QLQ-PR25) [46]. The disease- and treatment-related side effects are only a component of health-related quality of life [47]. To address the components of overall well-being, a general instrument is used in addition to the disease-specific questionnaires [48-50]. The RAND-36 assesses physical and social functioning, physical and emotional role restriction, mental health, vitality, pain, general health and change in health. The EORTC QLQ-C30 contains five functional scales, three symptoms scales, a global QoL scale and six single-items. The EORTC QLQ-PR25 assesses urinary, bowel and sexual symptoms and functioning, and the side effects of hormonal treatment. The first questionnaire is handed over to the patient one week before treatment at the Department of Radiation Oncology and the next questionnaires are sent to the patient every six months until 10 years after the completion of the treatment. It is important to measure QoL every 6 months after treatment, to be able to determine the point in time at which the QoL changes, for example due to side-effects after treatment.

For disease-specific survival, death with metastases is considered a death caused by the disease.

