### Data analysis

All analysis will be performed according to the intention-to-treat principle. Cox proportional hazards regression will be used to analyze differences in biochemical failure and disease-specific survival between the two treatment arms. Survival curves will be estimated by the Kaplan-Meier technique. Differences between both groups in the incidence of acute side-effects will be tested with the Chi square test. The incidence of late toxicity will be analyzed actuarially with the Kaplan-Meier method, the log rank test and Cox regression analysis. To analyze differences in QoL between the two treatment groups over the time points, a general linear model repeated-measures analysis of covariance will be performed [52]. A change of 10% (or in general, 0.5 standard deviation) of the scale width is perceptible to patients as a meaningful change [53]. Because of the multiple comparisons for the QoL items, the p-value is set at a conservative 0.01 for determining statistical significance [54]. For all other analyses, which do not include the QoL measures, a p-value of < 0.05 is considered statistically significant.

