## Discussion

The FLAME-trial is designed to investigate the effect of an ablative microboost to the macroscopic tumor for patients treated with external beam radiotherapy for prostate cancer.

Previous studies demonstrated that the rate of toxicity after high dose external beam radiotherapy with the use of accurate position verification is low and consequently high QoL is reported [34,63-66]. Planning studies showed that an ablative microboost to the macroscopic tumor was theoretically feasible within the currently used dose constraints for rectum and bladder [15,67,68]. Furthermore, a feasibility study of Singh *et al*. [20] reported excellent early toxicity after simultaneous integrated IMRT boost of 95 Gy to the intraprostatic lesions. As a result, with the use of optimal position verification combined with the currently used dose constraints, the toxicity in the experimental treatment arm with the ablative microboost of 95 Gy is expected to be acceptable.

Previous trials demonstrated a biochemical benefit of dose escalation. However, up to now none of the dose escalation trials were able to detect an improvement in disease specific or overall survival. However, all trials were designed for biochemical survival instead of overall or disease-specific survival due to the natural behavior of prostate cancer. For this reason the FLAME-trial is also powered for biochemical disease free survival. An improvement in local control without a proven benefit in overall survival is only acceptable when severe toxicity remains limited. Furthermore, to establish whether a benefit in biochemical failure free survival also counterbalances the negative aspects of dose escalation, such as a small increase in toxicity, it is important that QoL is taken into account. Therefore, repeated QoL measurements are performed in patients included in this trial.

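### Kaplan-Meier for the incidence of late toxicity over 10 years, with other-cause deaths censored, overstates the absolute risk in older men

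*Protocol article*

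**What the plan says.** In the protocol article, Data analysis, the late-toxicity method is explicit: "The incidence of late toxicity will be analyzed actuarially with the Kaplan-Meier method, the log rank test and Cox regression analysis". Secondary endpoints sets the schedule: "late toxicity (every six months until 10 years after treatment").

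For the other time-to-event outcomes, Data analysis says "Cox proportional hazards regression will be used to analyze differences in biochemical failure and disease-specific survival between the two treatment arms", followed by "Survival curves will be estimated by the Kaplan-Meier technique". Secondary endpoints adds one attribution rule: "For disease-specific survival, death with metastases is considered a death caused by the disease".

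The article names no competing-risks estimator and does not say how a death enters the late-toxicity analysis. Censoring at death is not written down. It is what the named methods imply when death is not an event. No 10-year horizon is stated for disease-specific survival itself.

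Table 1 describes the first 50 patients, all from one centre: median age 70.5 (quartiles 66.8-73.0) and 33 of 50 (66%) with cardiovascular disease. The article gives no characteristics for the full 566.

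**The concern.** Kaplan-Meier treats a censored man as still at risk, with the same future hazard as the men who remain under observation. That suits a man who is lost to follow-up. A man who has died cannot develop late toxicity, so one minus Kaplan-Meier estimates the risk in a population where nobody dies of anything else. The article names the target as incidence, which readers will take as the share of treated men who develop the problem. In men of about 70 followed for 10 years, the two quantities separate.

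The absolute level matters here. The Discussion makes limited severe toxicity a condition for accepting the boost, and Sample size considerations justifies the one-sided test by the increased toxicity risk in the experimental arm. Absolute toxicity rates will therefore be quoted when benefit is weighed against harm.

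**Working it through.** **The plan's own figure.** The one design figure is N = 566 for 80% power at one-sided 5%, with 64% and 74% free from failure at 5 years. Under exponential hazards, HR = ln(0.74)/ln(0.64) = 0.675. Required events = 4 × (1.645 + 0.842)² / (ln 0.675)² ≈ 160. With the stated 5-year accrual (half enrolled at 70% of the time), 3.5 further years of follow-up and 20% loss over 5 years, 283 per arm give about 162.6 expected events and 80.6% power. The figure reproduces. It concerns biochemical failure only and does not depend on how late toxicity is estimated.

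**Inputs for the late-toxicity check.**
- Horizon of 10 years: Secondary endpoints.
- Kaplan-Meier risks of 20% and 30%: assumed, because the article gives no toxicity rate.
- Other-cause mortality μ of 2%, 3% and 4% a year: assumed, because the article gives none. Over 10 years this is 1 − exp(−10μ) = 18%, 26% and 33%.
- Constant, independent hazards.

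**Formula.** With toxicity hazard λ = −ln(1 − KM)/T, the cumulative incidence is CIF(T) = λ/(λ + μ) × [1 − exp(−T(λ + μ))].

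**Example.** For KM = 20% at 10 years, λ = 0.0223. With μ = 0.02, CIF = 0.527 × 0.345 = 18.2%. With μ = 0.04, CIF = 0.358 × 0.464 = 16.6%.

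| Horizon | Kaplan-Meier risk | CIF, μ = 2% | CIF, μ = 3% | CIF, μ = 4% | Kaplan-Meier / CIF |
|---|---|---|---|---|---|
| 10 years | 20% | 18.2% | 17.4% | 16.6% | 1.10 to 1.20 |
| 10 years | 30% | 27.4% | 26.1% | 25.0% | 1.10 to 1.20 |
| 5 years | 20% | 19.1% | 18.6% | 18.2% | 1.05 to 1.10 |

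The last column is relative to the true incidence. As a share of the Kaplan-Meier value, the 10-year gap is about 9-17%.

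**Timing of events.** Let the cumulative toxicity hazard follow a Weibull shape, with other-cause mortality of 30% over 10 years and a Kaplan-Meier risk of 20%. The ratio is 1.11 for early toxicity (shape 0.5), 1.18 for constant hazard and 1.26 for late events (shape 2). The direction is the same throughout; only the size moves.

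**Difference between arms.** Take Kaplan-Meier risks of 20% and 25%, with equal other-cause mortality in both arms. At μ = 2%, the CIFs are 18.2% and 22.8%, a difference of 4.6 points. At μ = 4% they are 16.6% and 20.8%, a difference of 4.2 points. A 5-point excess is thus read slightly too large, with its sign unchanged.

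**The case against.** The strongest reply is that the comparison of the arms is sound. Log-rank and Cox compare cause-specific hazards validly when other deaths are censored, and overstated toxicity does not hide harm. Kaplan-Meier disease-specific survival is a conventional net quantity, misleading only when read as a real-world probability. The Kaplan-Meier curve for biochemical failure has the same feature, so an absolute benefit would also be read somewhat too high. All of this stands. It limits the point to absolute risks and rules out saying that the benefit-harm balance is tilted one way.

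The size is also open to challenge. The mortality and toxicity rates are assumptions, Table 1 covers 50 men at one centre, and the bias is about half as large at 5 years. An analysis plan that is not shown may say how deaths are handled. These are fair limits on the magnitude. They do not change the direction, because the article itself names Kaplan-Meier for an incidence.

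A reader might infer more: that deaths caused by treatment fall outside every survival endpoint. The article does not support this. The rule "For disease-specific survival, death with metastases is considered a death caused by the disease" says that such deaths count, not that only they count. A treatment death in a man with metastases would be an event under it. A fatal toxicity can also be recorded as severe, since severe means above grade 2 with no upper limit, and the data safety monitoring board reviews toxicity and clinical outcome.

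A reader might also take the Discussion to make overall survival the trial's benchmark: "An improvement in local control without a proven benefit in overall survival is only acceptable when severe toxicity remains limited". That sentence sets a condition on toxicity. The surrounding text explains why the trial is powered for biochemical outcome, and it promises no overall survival analysis.

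**Conclusion.** The point holds for the absolute risks. The article fixes Kaplan-Meier for the incidence of late toxicity over 10 years; if other-cause deaths are censored, as is usual, the reported risk will exceed the one patients experience. The same applies to prostate-cancer death when its curve is read as an absolute risk.

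Under constant, independent hazards and an assumed 2-4% other-cause mortality a year, the relative overstatement is about 10-20% at 10 years and 5-10% at 5 years. It is smaller if toxicity comes early and larger if it comes late. The primary analysis, the arm comparisons and the sample size are untouched. This is a correction to how absolute risks are reported and does not threaten the trial's main conclusion. No conclusion follows about missing treatment deaths, the disease-death definition or the lack of an overall survival endpoint.

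**What to change.** In Data analysis, replace Kaplan-Meier as the estimator of late-toxicity incidence with the Aalen-Johansen cumulative incidence, treating death without the toxicity as a competing event. Report prostate-cancer death in the same way, with death from other causes as the competing event. Keep the log-rank test and Cox regression for comparing arms, and label them as cause-specific.

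The cost is a change of analysis wording. Disease-specific survival already requires dates and causes of death, so no new data are needed. The one downside is comparability: published late-toxicity rates from older trials that used Kaplan-Meier will not be on the same scale, and a footnote should say so.

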### Sample size considerations

The statistical power of the study was calculated for the primary endpoint (five-year freedom from biochemical failure). Based on data of two randomized clinical trials [2,51] reporting the treatment results of patients treated with a radiation dose equal to the dose of the standard arm of our trial, we expect that the five-year freedom from biochemical failure of the standard arm will be approximately 64%. We expect that an additional ablative microboost to the macroscopic tumor will increase this number with at least 10%. A one-sided log rank survival power analysis shows that the length of follow-up after accrual of the last patient should be 3.5 years to detect a difference of 10% (64% and 74% free from biochemical failure after 5 years, in the control arm and experimental arm, respectively) with a power of 80% at a one-sided 5% significance level. This is under the assumption that the patients enter the study during an accrual period of 5 years, 50% of the enrollment is complete when 70% of the accrual time has past and that 20% of the patients in both arms are lost to follow-up during the follow-up period of 5 years. The reason to choose a one sided p-value is that, although extremely improbable, an increase in biochemical failure in the experimental arm would lead to the same action as no difference at all between the two treatment arms. This is because the experimental treatment will only be implemented if it is significantly better than the usual treatment, due to the increased toxicity risk in the experimental arm.

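### The QoL method named in the article usually analyses only men with a complete set of forms, which suits six-monthly forms, staggered entry and 20% expected loss badly

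*Protocol article*

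**What the plan says.** The Data analysis section of the Protocol article names the QoL method outright. "To analyze differences in QoL between the two treatment groups over the time points", it says, "a general linear model repeated-measures analysis of covariance will be performed". The significance level for QoL is 0.01, and a change of 0.5 standard deviation is taken as meaningful to patients. The same section opens with the rule that "All analysis will be performed according to the intention-to-treat principle".

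The schedule is in the section Secondary endpoints: "The first questionnaire is handed over to the patient one week before treatment", and "the next questionnaires are sent to the patient every six months until 10 years after the completion of the treatment". That makes 1 baseline form and 20 follow-up forms.

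The section Sample size considerations assumes that "20% of the patients in both arms are lost to follow-up during the follow-up period of 5 years", that "the patients enter the study during an accrual period of 5 years", and that "50% of the enrollment is complete when 70% of the accrual time has past". It sets follow-up after the last patient at 3.5 years.

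The article gives no QoL time window, no expected return rate and no missing-data method.

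**The concern.** Classical repeated-measures analysis of covariance in the general linear model needs a full vector of outcomes for each patient. In standard use, a man who lacks one form in the analysed window contributes nothing, however many others he returned. A 10-year, six-monthly schedule with staggered entry and acknowledged loss is close to the worst setting for that requirement. It also works against the article's own reason for six-monthly forms, which is to find out when QoL changes.

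The men left out may differ from those kept. Forms can stop because of toxicity, relapse or death, and a complete-case set may then look healthier than the randomised groups. The Discussion gives QoL the task of showing whether a biochemical gain outweighs added toxicity, and the Study design section blinds patients to protect this measurement. A QoL harm missed for lack of data would read as reassurance about the boost.

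**Working it through.** **Inputs**
- Follow-up forms (Secondary endpoints): 7 to year 3.5, 10 to year 5, 20 to year 10.
- Loss (Sample size considerations): 20% over 5 years. Extended at a constant rate, the share retained is 0.8^(t/5).
- Entry over 5 years, half enrolled at 70% of that time (0.7 × 5 = 3.5 years). The analysis falls at 5 + 3.5 = 8.5 years from start.
- Total 566, or 283 per arm (Abstract).
- Assumption: a return rate *c* per follow-up form, independent between forms. The article gives no rate. The baseline form is taken as complete because it is handed over in the department.

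**1. The plan's own figure.** There is none for QoL. The primary-endpoint sample size uses the same accrual and loss inputs, so it shows whether they are read correctly. The hazard ratio is ln 0.74 / ln 0.64 = 0.675. Events by Schoenfeld, one-sided 5%, power 80%: 4 × (1.645 + 0.842)² / (ln 0.675)² ≈ 160; Freedman gives 164. With exponential failure and loss and the stated accrual pattern (truncated-exponential entry), the event probabilities are 0.333 and 0.241. The total needed is 558 (Schoenfeld) or 572 (Freedman), against 566. The figure reproduces.

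**2. Share with every form, if all men could reach the window.** Share = 0.8^(t/5) × c^k, with k follow-up forms.

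| Window | k | Stated loss only | c = 0.95 | c = 0.90 | c at which half are complete |
|---|---|---|---|---|---|
| 3.5 years | 7 | 85.5% (484) | 60% (338) | 41% (232) | 92.6% |
| 5 years | 10 | 80% (453) | 48% (271) | 28% (158) | 95.4% |
| 10 years | 20 | 64% (362) | 23% (130) | 8% (44) | 98.8% |

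**3. A 5-year window at the planned analysis.** At 8.5 years, only men who entered in the first 3.5 years, 50% of the total, can have 5 years of follow-up.
- No skipped form: 0.5 × 0.8 = 0.40, and 0.40 × 566 ≈ 226.
- c = 0.95: 0.5 × 0.8 × 0.95^10 = 0.5 × 0.8 × 0.599 = 0.239, about 135 men.
- No man can have a 10-year series at that time.

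The 40% is a ceiling. Form dates run from the end of treatment, which takes them slightly later than 5 years from entry.

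**4. What an all-forms analysis would hold at year 5.** At c = 0.95, men with a year-5 form number 0.5 × 0.8 × 0.95 = 0.38, and 0.38 × 566 ≈ 215, against 135 with complete series. The earlier forms of everyone else are used as well.

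**5. Power.** For a simple two-arm comparison of 0.5 SD, two-sided 0.01 (sidedness for QoL assumed), n per arm: Φ(0.5 × √(n/2) − 2.576).
- 566 men: 99.96%
- 226 men: 88%
- 135 men: 63%

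The first figure is an upper bound. No method has year-5 data on all 566 at the planned analysis.

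**6. Bias.** In an illustrative simulation the true 5-year difference was set at −5 points and dropout was made to depend on the previous score. Under strong dependence, the complete-case estimate was about −4.8 with 80% kept and −4.6 with 40% kept. When dropout was unrelated to QoL it was essentially unbiased.

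**The case against.** The strongest reply is that the article does not say incomplete series are dropped. It fixes no window and no list of visits, and its full protocol or analysis plan may specify imputation or a few set visits, either of which would remove much of the loss. This stands as a limit on the size. It does not remove the point, because the article itself chooses the method, and the choice suits the design badly.

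A reader might infer that most men will be discarded. The documents do not support that in general. Stated loss alone leaves 80% complete at 5 years, and a 3.5-year window keeps more than half if return exceeds about 92.6% per form. Independent skipping is also pessimistic. With the same 95% average return and modest clustering within men (assumed beta-binomial, correlation about 0.09), 55% rather than 48% are complete at 5 years. Moreover, the 3.5-year follow-up is set for biochemical failure; nothing schedules a 5-year QoL analysis then, and waiting would remove the halving. Neither clustering nor high return, however, can lift the 40% ceiling if that analysis is done at that time.

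A reader might also infer that the comparison is biased. That is a risk only. Late entry is largely non-informative, and the simulated bias was small.

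Nor does the method plainly break intention to treat. Missing outcomes do not contradict analysis by allocated arm, and a mixed model also omits men with no usable form. Sphericity is minor, since multivariate tests and standard corrections are available.

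**Conclusion.** The point holds as a criticism of a stated method. Repeated-measures analysis of covariance in its usual form needs complete series, and this trial's schedule, entry pattern and assumed loss ensure that many series will be partial.

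For a 5-year window at 8.5 years from start, at most about 40% of men can be complete. This rests on the article's figures alone, apart from the choice of window and timing. The 24% figure adds an assumed 95% independent return. A shorter window or a later analysis loses fewer. Bias is possible where missing forms follow toxicity, relapse or death; its direction and size cannot be established from the article.

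QoL is a secondary endpoint, and the primary analysis and its sample size are untouched. Because QoL is meant to weigh harm against benefit, the change should still be made.

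**What to change.** Replace the sentence with a likelihood-based linear mixed model for repeated measures on all returned forms. Fixed effects: arm, visit, arm-by-visit, baseline score, and the stratification factors TURP, hormonal treatment and centre. State the time window and report arm differences at set visits.

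Use an unstructured within-patient covariance only for a limited set of visits. Over 20 follow-up visits it would need 20 × 21 / 2 = 210 parameters, so a parsimonious structure is preferable there.

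Add a missing-data sensitivity analysis. The mixed model relies on missingness being explained by the observed data, and it does not by itself settle how QoL after death is to be read.

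The cost is one reworded sentence and slightly more analysis work in standard software. No new data are needed.
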